## Abstract

**Background:**

Staff absenteeism and presenteeism incur high costs to the NHS and are associated with adverse health outcomes. The main causes are musculoskeletal complaints and mental ill-health, which are potentially modifiable, and cardiovascular risk factors are also common. We will test the feasibility of an RCT to evaluate the clinical and cost-effectiveness of an employee health screening clinic on reducing sickness absenteeism and presenteeism.

**Methods:**

This is an individually randomised controlled pilot trial aiming to recruit 480 participants. All previously unscreened employees from four hospitals within three UK NHS hospital Trusts will be eligible. Those randomised to the intervention arm will be invited to attend an employee health screening clinic consisting of a screening assessment for musculoskeletal (STarT MSK and STarT Back), mental (PHQ-9 and GAD-7) and cardiovascular (NHS Health Check if aged ≥ 40, lifestyle check if < 40 years) health. Screen positives will be given advice and/or referral to recommended services. Those randomised to the control arm will receive usual care. Participants will complete a questionnaire at baseline and 26 weeks; anonymised absenteeism and staff demographics will also be collected from personnel records. The co-primary outcomes are as follows: recruitment, referrals and uptake of recommended services in the intervention arm. Secondary outcomes include the following: results of screening assessments, uptake of individual referrals, reported changes in health behaviours, acceptability and feasibility of intervention, indication of contamination and costs. Outcomes related to the definitive trial include self-reported and employee records of absenteeism with reasons. Process evaluation to inform a future trial includes interviews with participants, intervention delivery staff and service providers receiving referrals. Analyses will include presentation of descriptive statistics, framework analysis for qualitative data and costs and consequences presented for health economics.

**Discussion:**

The study will provide data to inform the design of a definitive RCT which aims to find an effective and cost-effective method of reducing absenteeism and presenteeism amongst NHS staff. The feasibility study will test trial procedures, and process outcomes, including the success of strategies for including underserved groups, and provide information and data to help inform the design and sample size for a definitive trial.

**Trial registration:**

ISRCTN reference number 10237475.

## Introduction

The National Health Service (NHS) in the UK is one of the top ten employers in the world, with 1.3 m employees [1]. However, sickness absenteeism costs the NHS approximately £2.4 billion per year [2], with an annual average of just under 10 absence days per employee [3]. In 2016, this was 46% higher than other UK industries and 27% higher than the average in the public sector [4, 5] and is associated with worse patient outcomes [2, 6–10]. For example, there is an established link between staff mental illness and poor patient outcomes such as patient satisfaction and medication errors [11–13]. A greater potential cost is that of presenteeism (attending work whilst unwell) [14–16], with 56% of NHS staff in 2009 reporting pressure to attend work when feeling unwell [17]. Workers often cycle between absenteeism and presenteeism.

The main cause of sickness absenteeism in the NHS is mental ill-health at 25.4% of all recorded days lost in 2019, nearly double that of 2010 [18] and peaking at 32.4% during the first wave of the COVID-19 pandemic [19]. This is followed by musculoskeletal (MSK) complaints affecting 16% [20]. Poor lifestyle (smoking, lack of physical activity) and overweight/obesity are also important independent determinants of absenteeism [21–25] and presenteeism [26–28], with cardiovascular disease being up to five times greater amongst staff over 50 years old (unpublished local NHS data) [29]. Absenteeism varies by occupational group, being highest in the lowest paid (healthcare assistants), professions allied to medicine and infrastructure support staff [30]. Presenteeism rates follow similar patterns [31]. Since the pandemic, rates of absenteeism have risen, and reports of mental ill-health have increased [32].

In response to the high levels of staff ill-health and absenteeism, NHS England created a “Healthy Workforce Programme”, supported by the Royal College of Physicians [33], with a £450 m financial incentive for Trusts to improve staff health and well-being and thereby patient care [34]. Key actions included making the NHS cardiovascular disease (CVD) health check (for those aged 40–74 years without pre-existing diabetes or CVD) [35] more accessible for staff in the workplace and improving access to physiotherapy, mental health, weight management and smoking cessation services [36]. In most hospitals, occupational health services, which are often outsourced, do not have a preventive or well-being role, and therefore, new initiatives are required.

There are several systematic reviews and many individual studies which evaluate the effectiveness of workplace health promotion or return-to-work programmes [27, 37–39], but few are conducted amongst healthcare staff, and they rarely consider impact on absenteeism or presenteeism or include a control group. None has evaluated the cost-effectiveness of interventions targeted at screening for and early management of the main causes of absenteeism in healthcare settings — essential evidence before Trusts will invest limited healthcare resources. The evidence available reinforces the need to focus on high-risk groups, provide interventions of sufficient intensity and optimise attendance to maximise the chances of interventions being effective [40, 41]. The most effective model is likely to be a combination of health screening and health/wellness programmes with targeted interventions [42]. Based on learning from a previous pilot self-referral employee health screening clinic set up at the Queen Elizabeth Hospital Birmingham (QEHB), we have developed a health screening service for hospital employees, including pathways for direct invitation, assessment for CVD, MSK and mental health problems (the three major causes of staff absenteeism) and onward referral. The pilot clinic demonstrated that 41% of attendees were overweight, 18% obese, 27% inactive, 12% were smokers, 11% had hypertension and 11% high cholesterol, 13% had moderate and 10% severe anxiety and 8% had moderate and 4% severe depression. Overall, around a third required at least one onward referral (unpublished data). However, the clinic had poor engagement from lower paid staff, ethnic minorities and night shift workers, and therefore, a more inclusive approach to promotion of the service is required to be fully effective. We present the protocol of a pilot randomised controlled trial (RCT) to assess the feasibility of conducting a full RCT to evaluate this service in reducing absenteeism and presenteeism, as well as to evaluate its cost-effectiveness.

## Methods

### Aims and objectives

The aim of this pilot trial is to test the feasibility of a definitive RCT evaluating the clinical and cost-effectiveness of a complex intervention (health screening clinic), compared to usual care, in reducing absenteeism and presenteeism amongst NHS staff.

Objectives for the feasibility study are as follows:Describe recruitment rates.Describe participant characteristics and assess generalisability compared to the hospital workforce.Describe screening assessment results.Describe recommended referrals and their uptake.Assess the feasibility of measuring the primary and secondary outcomes and obtain information to inform the sample size for a full RCT.Assess levels of contamination between intervention and usual care arms.Describe and explain the fidelity to the intervention and evaluate views, experiences and acceptability of participants and intervention delivery staff.Explore the feasibility of such a service in other NHS and external settings, e.g. ambulance service, GP (general practitioner) practices and commercial organisations, explored in the process evaluation.Quantify the costs of undertaking the screening service and its consequences.

### Design and setting

A multicentre, parallel group, open, individually randomised pilot RCT of a complex intervention comparing an employee health screening clinic with usual care in four NHS Hospital Trusts in the West Midlands, including three large urban hospitals and one rural district general hospital (Table 1). This provides good generalisability and allows testing practicality in a range of sites. On balance, we have chosen an individually randomised trial as we feel this is more feasible, requiring fewer participants and fewer hospitals. We anticipate risk of contamination to be low as the full screening assessment, and tailored individual recommendations will only be accessible by invite and subsequent participation in the intervention arm of the trial. However, this will be assessed in the trial to decide whether a cluster trial is warranted instead.

**Table 1 Tab1:** Description of study sites

Hospital	Staff	Setting
Queen Elizabeth Hospital Birmingham (QEHB) (University Hospitals Birmingham (UHB) NHS Foundation Trust)	9000	The largest single site hospital in the country. Regional centre for cancer, largest solid organ transplantation programme in Europe, a regional Neuroscience and Major Trauma Centre and includes The Royal Centre for Defence Medicine.
Heartlands hospital (University Hospitals Birmingham NHS Foundation Trust)	11000	Includes four secondary care city-based hospital sites (Heartlands, Good Hope, Solihull and the Chest Clinic), one of the top five employers in the West Midlands. We will focus on the Heartlands site
Birmingham Children’s Hospital (Birmingham Women’s and Children’s NHS Foundation Trust)	6000	Secondary and tertiary care hospital serving 384,000 women and children annually
Hereford hospital (Wye Valley NHS Trust)	3000	One of the smallest rural district general hospitals in England, serving a population of 180,000

### Participants, eligibility, recruitment and consent

All employees in the participating hospitals who are able to provide informed consent will be eligible to participate except those who have previously attended a pilot clinic at QEHB or who are currently taking part in another intervention trial.

In order to be accessible to the full workforce and promote equitable recruitment of participants on gender, race, staff group and staff grade, participants will be invited through multiple approaches including email, information on payslips, mail outs, personal invitation, staff meetings, noticeboards and ward champions, in several phases, designed as far as possible to reflect the workforce characteristics of each hospital. Departmental recruitment information will be collected, so we can analyse how the trial was promoted across the Trusts. Reminder letters will be sent to nonresponders after 2 weeks and a further two if necessary. Posters advertising the trial will be displayed in departments/wards for a minimum of 2 weeks (or more if local arrangements require) before invitations are sent out during which time staff can request not to receive an invitation. Local staff will be engaged to raise trial awareness and arrange cover to allow attendance.

Consent will be obtained electronically online, on participants’ own electronic devices or with the help of trial staff at the health screening clinic. The participant information sheet will be available on the study website and in paper format; participants may contact the research team by telephone or request contact from the research team via the trial website to ask any questions. Consent will be confirmed at each follow-up appointment.

### Data collection and management

Table 2 shows the data collection schedule for participants. Study data will be entered into a REDCap1^1^ (Research Electronic Data Capture) database custom designed and hosted by the University of Birmingham either directly by participants or the clinic staff [43, 44]. Participants will complete the baseline questionnaire at a time convenient to them. Prompts will be sent after 24 h, 2 days and 7 days where the baseline questionnaire remains incomplete.

**Table 2 Tab2:** Schedule of assessments

Visit	Eligibility screening, consent and randomisation	Baseline	Intervention screening visit	26-week follow-up data collection	Between baseline and 26 weeks
Timeframe for follow-up data collection				+/−4 weeks	
Trial registration	x				
Consent to eligibility screening	x				
Eligibility screening	x				
Participant information and contact details	x				
Valid informed consent	x				
Staff payroll number	x				
NHS number (optional)	x				
Demographics (DOB, gender, education, marital status)		x			
Smoking status		x		x	
Exercise level (GPPAQ questionnaire)		x	x	x	
Ethnicity		x			
Diagnosed medical conditions		x			
Current medications		x			
Health status (EQ-5D questionnaire)		x		x	
Height		x			
Weight		x		x	
Health service utilisation		x		x	
Current employment		x		X	
Absenteeism and presenteeism (WHO-HPQ questionnaire)		x		x	
Occupational health resource utilisation		x		x	
Randomisation	x				
**Health screening (intervention group only)**					
**Musculoskeletal health (if applicable)**					
STarT Back screening tool (participant completion)			x		
STarT Back screening tool (review)			x		
STarT MSK screening tool (participant completion)			x		
STarT MSK screening tool (review)			x		
OMPSQ tool (participant completion)			x		
OMPSQ tool (review)			x		
Impact on work questions: musculoskeletal health			x		
**Mental health (if applicable)**					
GAD7 questionnaire (participant completion)			x		
GAD7 questionnaire (review)			x		
PHQ9 questionnaire (participant completion)			x		
Impact on work questions; mental health			x		
**Cardiovascular health (if applicable)**					
Personal details checked from baseline (age, ethnicity)					
BMI			x		
Smoking status (review from baseline questionnaire)			x		
Alcohol intake (review of AUDIT C questionnaire)			x		
Exercise level (review of GPPAQ questionnaire)			x		
Cardiovascular risk calculator (QRISK2 score)			x		
**Clinical measures (if age > = 40 years)**					
ECG			x		
Pulse			x		
Blood pressure			Up to 3 readings		
Blood tests (criteria for taking blood must be met)			x		
Cholesterol			x		
HbA1C (if indicated as per NHS Health Check)			x		
eGFR (if indicated as per NHS Health Check) (calculated using creatinine or U&Es, according to Trust policy)			x		
Recommendations from the health screening clinic (intervention group only)				x	
Recently diagnosed health conditions				x	
Trust staff characteristics	x				
Trust absenteeism rates	x				
Participant absenteeism data	x			x	
**Process evaluation (if applicable)**					
Valid informed consent					x
Qualitative interview/focus group					x

Self-reported data will be collected on all participants prior to randomisation, but after consent, including the following: contact details, demography, employment details, selected diagnosed medical conditions and current medications, absenteeism (World Health Organisation Health and Work Performance Questionnaire — WHO-HPQ) [45], presenteeism (WHO-HPQ) [45], health-related quality of life (HRQoL EuroQol 5 level — EQ-5D 5L) [46], smoking status, height, weight, exercise levels (General Practice Physical Activity Questionnaire — GPPAQ) [47], receipt of NHS Health Check and health service utilisation. We will also collect NHS number where available (this is optional) to allow (and assess the feasibility of) future linkage to routine data such as hospital admissions, general practitioner (GP) records, other healthcare utilisation and mortality data. Consent will be obtained to collect the following data from human resources (HR) records:Participant age, sex, ethnicity, staff group and staff gradeNumber of hours contracted to workHours worked — full-time equivalentSickness absenteeism and non-sickness absences relating to COVID-19 only, for the previous 24 months and follow-up (start/end dates, duration in days, recorded reason)Leaving date (should participant leave employment of the Trust during trial participation)

At 26 weeks, participants will be sent a follow-up questionnaire for online completion to report uptake of any recommended services (intervention arm only) and other outcomes as detailed below. Linked personnel data will be obtained on all consented patients including absenteeism at 26-week follow-up to allow comparison pre/post intervention.

Additional anonymised data will be collected at the time of site set-up from hospital HR records, at whole hospital level and for those invited and on age, sex, ethnicity, job role, days and reasons for absenteeism, in order to assess the generalisability of the included participants.

Respondents will also be provided with the option to provide reasons for taking/not taking part in the study. This will be anonymised.

### Allocation to trial arm

On completion of the baseline questionnaire, clinic staff will receive an alert to check eligibility criteria and consent, and participants will then be randomised to intervention or control arm. Randomisation will be at the level of the individual in a 1:1 ratio, using a minimisation algorithm to ensure balance on the following variables: age, sex, self-reported job categories, nightshift work and centre. To avoid predictability, a “random element” will be included in the minimisation algorithm. Given the nature of the intervention, blinding will not be possible.

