### Outcomes

#### Primary outcomes and stop/go criteria

There are three co-primary outcomes:Recruitment (consented) as a proportion of those invitedDirect referral to any recommended services as a result of the three screening components (usually GP, physiotherapy, community psychological services depending on local pathways at the time of the study) (intervention arm only)Attendance at any recommended services (self-report at 26 weeks, intervention arm only)

These will inform criteria to progress to the definitive trial (Table 3).

**Table 3 Tab3:** Progression criteria informing decision about full trial

		Progression criteria		
	Description	Green (go)	Amber (pause)	Red (stop)
Recruitment^a^	% of invited employees consenting to take part	> 25%	15–25%	< 15%
Referred directly to a service^b^	% of participants randomised to intervention arm referred to specified services Measured at 26 weeks	> 30%	10–30%	< 10%
Attendance at referrals^c^*	% of referrals which resulted in self-reported attendance at the service at least once. Measured at 26 weeks	> 50%	30–50%	< 30%
**Action**		**If ALL criteria are GREEN, proceed to full trial with protocol unchanged**	**If ANY of these criteria are AMBER, adapt protocol appropriately using information from the process evaluation before proceeding to full trial**	**If ALL of these criteria are RED, consider whether current protocol is not feasible** **If ONE OR TWO of these criteria are RED, consider whether adaptations are needed**

^a^A recent study of low-paid government workers receiving an NHS Health Check in the workplace demonstrated benefits to cardiovascular health with 20% uptake of the intervention [60] and experience from a primary care COPD screening trial with > 35% uptake [61] and primary care cohort with > 25% uptake [62]. ^b^A feasibility study of a cardiovascular health check in an NHS hospital showed that 33% required follow-up with a GP or other health professionals [63]; experience from our pilot clinic with cardiovascular and mental health checks showed that 35% required further follow-up. ^c^The feasibility study mentioned above also showed that 54% of those referred to further services had attended within 5 weeks, and most of the remainder intended to do so [63]. *We will present both % of referred participants attending at least one of their referrals (at least once) and % of total referrals resulting in an attendance

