### Process evaluation

A mixed-methods process evaluation will explore programme reach; fidelity of screening delivery; attendance at referrals; participants’ views of the intervention; views and experiences of the training received by those delivering the intervention, its acceptability and satisfaction with the intervention overall; and views of providers of follow-on services, e.g. GPs and “healthy minds”. In addition, we will explore the views of potential beneficiaries, e.g. other NHS organisations who might be willing to run the trial such as ambulance services and GP groups and private, non-healthcare organisations who might be interested in delivering and evaluating such a service for their setting.

Quantitative data to support the process evaluation will be obtained from the following:*Recruitment and follow-up data*, e.g. response rate; proportions of those invited consenting, being randomised and attending the screening; follow-up at 26 weeks*Baseline questionnaire* to assess characteristics, e.g. data on age, ethnicity, marital status, Index of Multiple Deprivation, educational attainment and employment role of the employees recruited to study (programme reach)*Logs* kept by the staff health screening programme recording attendance, screening tests undertaken and duration of contacts (fidelity)*Healthcare issues* identified at the employee screening and referrals made to GP and other services (fidelity)*Self-report of attendance at recommended services* from follow-up questionnaires (uptake)*Brief questionnaire to staff* not taking up the offer of the study to ascertain reasons for not participating and a question to participants to ascertain which recruitment method most prompted them to participate (reach)

Focused qualitative interviews lasting approximately 30 min either face to face, by voice over Internet protocol (e.g. zoom) or telephone according to participant preference will be conducted with the following:Up to 40 participants, sampled on age, gender and ethnicity, occupation, site, shift pattern and department, selected from those randomised.

Those in the intervention group are as follows:A.Did not attend screeningB.Did not need referral to other servicesC.Needed referral to other services

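### The recruitment progression criterion counts consent, not randomisation, so no threshold registers consenters who never complete the baseline questionnaire

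*Protocol article*

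**What the plan says.** In the protocol article, the section on primary outcomes and stop/go criteria defines the first co-primary outcome as consented employees over those invited. Table 3 repeats this as the percentage "of invited employees consenting to take part", with GREEN above 25%, AMBER 15–25% and RED below 15%.

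The order of events is set elsewhere. Under Data collection and management (text after Table 2): "Self-reported data will be collected on all participants prior to randomisation, but after consent". The section headed Allocation to trial arm gives the next step: "On completion of the baseline questionnaire, clinic staff will receive an alert to check eligibility criteria and consent, and participants will then be randomised". Participants fill in the baseline questionnaire when it suits them, and non-completion is foreseen: "Prompts will be sent after 24 h, 2 days and 7 days where the baseline questionnaire remains incomplete".

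The second Table 3 criterion has a different starting point, the percentage "of participants randomised to intervention arm referred to specified services". The action for a fully GREEN result is: "If ALL criteria are GREEN, proceed to full trial with protocol unchanged". The Process evaluation section lists the "proportions of those invited consenting, being randomised and attending the screening" among its quantitative data, with no threshold attached.

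**The concern.** A definitive trial compares randomised arms, so the recruitment rate it depends on is randomised/invited. Everyone randomised has consented, so consented/invited can equal or exceed that rate but never fall below it. Any discrepancy therefore favours progression.

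The three criteria also leave a gap. The first ends at consent and the second begins at randomisation. A consenter lost in between helps the first criterion and is absent from the second. If all three are GREEN, Table 3 points to an unchanged protocol, and it calls on process-evaluation information explicitly only under AMBER. At stake is whether the rule would prompt a look at the step from consent to randomisation when recruitment is near its 25% boundary.

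**Working it through.** **The plan's own figure.** The Sample size section gives a 95% confidence interval of 21% to 29% for a 25% recruitment rate with 480 participants. The Wald interval is 0.25 ± 1.96 × √(0.25 × 0.75 / 480) = 0.25 ± 0.0387, or 21.1% to 28.9%. The figure reproduces with 480 as the denominator. It does not show whether the 480 are consenters or randomised participants.

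**Inputs.** The 25% and 15% cut-offs come from Table 3 and the 480 from Sample size. The loss between consent and randomisation, d, is not given in the article, so I assume 5% to 20%.

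**Formulas.** With consent rate c:
- randomised/invited = c × (1 − d)
- the consent criterion reads GREEN while randomised/invited is 25% or less when 25% < c ≤ 25% / (1 − d)
- consents needed to randomise 480 = 480 / (1 − d), rounded up

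| Assumed loss d | Top of the affected consent range | Randomised/invited if c = 26% | Randomised if 480 consent | Consents needed to randomise 480 |
|---|---|---|---|---|
| 5% | 26.3% | 24.7% | 456 | 506 |
| 10% | 27.8% | 23.4% | 432 | 534 |
| 15% | 29.4% | 22.1% | 408 | 565 |
| 20% | 31.3% | 20.8% | 384 | 600 |

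The fourth column applies only if the 480 are consenters, which the article does not say.

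**Loss that turns GREEN into AMBER.** Setting c × (1 − d) = 25% gives d = 1 − 25%/c:
- c = 26%: 1 − 25/26 = 3.8%
- c = 28%: 1 − 25/28 = 10.7%
- c = 30%: 1 − 25/30 = 16.7%
- c = 35%: 1 − 25/35 = 28.6%

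**Loss that brings GREEN down to the RED boundary.** At c = 26%, d = 1 − 15/26 = 42.3%. A change of that size is not realistic within the assumed range, so the issue is GREEN against AMBER.

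The affected range is 1.3 to 6.3 percentage points wide. A small loss matters just above 25%, and only a large one matters at 35%.

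**The case against.** **The definition is open and consistent.** The outcome and Table 3 agree that consent is the numerator, and willingness to take part is a coherent thing to measure. This stands: the point is a badly chosen numerator, not a contradiction.

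**The cut-offs were set for uptake, so a narrower numerator tightens the rule without justification.** This stands only in part. The first benchmark in Table 3 footnote a is uptake of the intervention, which lies further along the pathway than consent, so keeping the cut-offs for randomised/invited is not unreasonable.

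**The article condenses protocol version 5.0, which may define a recruited participant more fully.** That may be so, but the article does fix the numerator as consent, in two places.

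A reader might also infer several stronger points that the article does not support:

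- *That it is unclear which consent counts*, because Table 2 also lists "Consent to eligibility screening". Table 3 refers to consent to take part, which settles it.
- *That many consenters will fail the eligibility check.* Table 2 puts eligibility screening in the same column as consent and randomisation, and the exclusions are few. The later staff check may be mere verification. Unfinished questionnaires are the likelier source of loss.
- *That the prompts show loss is expected.* They show that incomplete questionnaires are foreseen and are also a means of reducing loss. They say nothing about how much remains.
- *That the definitive trial's invitation numbers will be set too low.* Randomised/invited is among the process-evaluation data, so planners will have it.
- *That the loss can never lead to a change.* Table 3 informs a decision, and those overseeing the trial can see the process data. What holds is narrower: no progression threshold registers the loss.

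**Conclusion.** The point holds in this limited form. The recruitment criterion ends at consent, trial entry requires a completed baseline questionnaire and a staff check, and the next criterion starts from those randomised. Loss between the two has no threshold and can only make recruitment look better.

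The size is conditional. Under an assumed loss of 5% to 20%, consent rates from just above 25% up to 26.3% to 31.3% would read GREEN where randomised/invited is AMBER. If the loss is negligible, or consent is well above this range, the classification does not change. Even inside the range, the action changes only if the other two criteria are also GREEN, because any AMBER already calls for adaptation. The consequence is then a missed prompt to adapt the protocol before the full trial. The pilot's validity is not affected.

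**What to change.** Define the Table 3 recruitment row and co-primary outcome 1 as the percentage of invited employees who are randomised, keeping the existing cut-offs. Report consented/invited and randomised/consented beside it, so that reluctance to join can be told apart from loss at the baseline questionnaire. State in Sample size that the 480 are randomised participants.

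The article reports that recruitment was still under way at submission. If the co-primary outcome is therefore left as consent, apply the Table 3 decision to randomised/invited as well.

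No new data are needed, since the process evaluation already plans the counts. The costs are a slightly stricter criterion, a slightly less favourable recruitment figure, and a change to a progression rule during recruitment that must be dated and documented. If the 480 had been meant as consenters, counting randomised participants would also require 506 to 600 consents under the assumed 5% to 20% loss.
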